### Immunological measurements

To analyze the effect of the treatment on cytokine production, we will determine the in vitro capacity of peripheral blood mononuclear cells to produce cytokines. Heparinized blood (15 ml) will be drawn before, after two and after three months of treatment, or at earlier withdrawal. Peripheral blood mononuclear cells will be isolated by centrifugation of Ficoll isopaque. T cell cytokine production will be stimulated by incubation of cells with anti-CD28 and anti-CD2 monoclonal antibodies and supernatants will be collected after 48 hours of culture. In addition, adherent cells (monocytes/macrophages) will be stimulated for 24 hours with lipopolysaccharide to induce IL-6 and IL-12 production. Cytokine levels in culture supernatants will be analyzed by ELISA. In vivo cytokine production will be analyzed by determining cytokine levels in plasma samples obtained at the same time points. In addition, blood will be stored for future research possibilities on the immunological or genetic aspects of schizophrenia, schizoaffective and schizophreniform disorders, after permission of the patients (in the informed consent form).

### Withdrawal from the study

A patient must be withdrawn from the study when judged necessary by the responsible psychiatrist or when the patient withdraws his/her informed consent. In these instances all outcomes should be assessed.

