### Study outcomes

The primary outcome of this trial is the 3-month change in positive and negative symptoms on the total PANSS score. Secondary outcomes are the 3-month change in the PANSS subscales, cognitive symptoms, immunological parameters (γ-interferon, IL-4, IL-6 and IL-12), and psychoactive medication taken during the trial.

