### Follow-up assessments

At one, two, and three months, and in case of withdrawal from the study, the severity of positive and negative symptoms will be reassessed using the PANSS. The cognitive tests will be repeated at three months or at study discontinuation. Blood samples will be taken at 2 and 3 months, or at withdrawal, for determination of the Aspirin levels. All assessments will be performed blind to medication status. The overview of the visits can be seen in table 1.

**Table 1 T1:** Overview of assessments/interventions

	Start of run-in	Baseline	1 Month	2 Months	3 Months (@)
Informed Consent	X	-	-	-	-
Screening	X	-	-	-	-
Pregnancy test	X	-	-	-	-
Randomization	-	X	-	-	-
Immunological parameters	X	-	-	X	X
Blood for DNA isolation	X	-	-	-	-
Aspirin concentration	-	-	-	X	X
PANSS	-	X	X	X	X
CASH (+)	X	-	-	-	-
Cognitive tests	-	X	-	-	X
Adverse events	-	-	X	X	X
Co-medication	X	X	X	X	X
Compliance	-	X	X	X	X

@ or withdrawal

+ if previous CASH is longer than 6 months ago

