### Data analysis

The statistical significance of the difference in the change in total PANSS score, its subscores, cognitive functions, immunological parameters from baseline to last follow-up between the arms and psychoactive medication will be tested using a two-sided unpaired t-test and its magnitude will be supplied with a 95% confidence interval. In addition, all outcomes will be analyzed as dependent variables in repeated measurements analyses with treatment arm as the independent variable. To study whether the potentially beneficial effect of acetylsalicylic acid is modified by initial relative TH-2 reactivity, we will repeat the analyses in strata of IFN-γ/IL-4 ratio The analyses will primarily be 'intention-to-treat'. In addition, a per protocol analysis will be performed on those who showed more than 90% adherence. If despite randomization important baseline differences in prognostic factors exist, adjustments will be made by including the corresponding variables as independents in the multivariable models. Finally, the change in psychopathological symptoms will be related to the change in immunological parameters using multivariable regression models. In these analyses adjustments for confounders will be made when appropriate.

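### Patients withdrawn by the psychiatrist who still consent have no scheduled month-3 PANSS, so an early exit score stands in for the 3-month outcome in the intention-to-treat comparison

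*Protocol article*

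**What the plan says.** All references are to the protocol article, under Design and methods.

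- **Withdrawal from the study.** There is one exit route with two triggers: "A patient must be withdrawn from the study when judged necessary by the responsible psychiatrist or when the patient withdraws his/her informed consent". One instruction covers both: "In these instances all outcomes should be assessed".
- **Follow-up assessments, Table 1.** The footnote to the 3-month column reads "or withdrawal". The text above the table puts cognitive tests at month 3 or at discontinuation. For PANSS it lists months 1, 2 and 3 *and* withdrawal.
- **Immunological measurements.** Blood is drawn at two and three months, or at an earlier withdrawal.
- **Study outcomes.** "The primary outcome of this trial is the 3-month change in positive and negative symptoms on the total PANSS score".
- **Data analysis.** The t-test on total PANSS and the other outcomes takes change to the last follow-up; the sentence includes the words "immunological parameters from baseline to last follow-up between the arms". In addition, "all outcomes will be analyzed as dependent variables in repeated measurements analyses with treatment arm as the independent variable". The section continues: "The analyses will primarily be" intention-to-treat.
- **Study size.** The calculation also uses change to last follow-up, with 40 per arm and a 10% allowance for withdrawal.

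**The concern.** The psychiatrist's decision and the patient's withdrawal of consent have different consequences for data collection. After the first, the patient may be willing and able to attend at month 3. After the second, nothing further can be expected without the patient's agreement. The plan handles them alike, and the exit visit takes the place of month 3 in both.

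The outcome section asks for the change at three months, while the analysis takes whatever score came last. For a patient withdrawn after a few weeks these are different quantities. Withdrawal on clinical judgement is plausibly related to how the patient is doing, and possibly to arm through tolerability. At stake are dilution of the effect if withdrawal is similar in both arms, and bias if it is not. A later analysis plan cannot recover visits that were never scheduled.

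**Working it through.** **1. Reproduce the plan's own figure.** Inputs from Study size: d = 0.66, two-sided alpha 0.05, power 0.80, unpaired t-test, 10% withdrawal.

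- Per arm, normal approximation: 2 × (z₀.₉₇₅ + z₀.₈₀)² / d² = 2 × 7.849 / 0.4356 = 36.04.
- Inflated for withdrawal: 36.04 / 0.9 = 40.04 per arm, so 80 in total.

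The stated 80 reproduces and is not in question. The calculation treats the 10% (0.10 × 80 = 8 patients, 4 per arm if equal) as contributing no data. The withdrawal and analysis sections keep them in through an exit score.

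**2. Trace one patient.** Take a patient withdrawn by the psychiatrist between months 1 and 2 who still consents. The PANSS scores are baseline, month 1 and exit.

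| Use | Value available |
|---|---|
| 3-month change (Study outcomes) | not observed |
| Change to last follow-up (Data analysis) | exit minus baseline |
| Repeated-measurements analysis | month 1 and exit; month 3 only through a missing-at-random assumption |

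**3. Dilution.** Assumptions not in the document: the same share w withdraws in each arm, exit scores carry a fraction f of the month-3 effect, the SD is unchanged, and 40 per arm are analysed.

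Effect tested: d* = 0.66 × (1 − w + w·f). Power is from the noncentral t.

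- Complete month-3 data: d = 0.66, power 0.830.
- w = 0.10, f = 1/3: d* = 0.66 × 0.9333 = 0.616, power 0.777.
- w = 0.20, f = 1/3: d* = 0.66 × 0.8667 = 0.572, power 0.714.
- w = 0.30, f = 1/3: d* = 0.66 × 0.80 = 0.528, power 0.645.

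Range for f from 0 to 2/3: power 0.747 to 0.805 at 10% withdrawal, and 0.645 to 0.777 at 20%.

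**4. Bias with no treatment effect.** Assumptions not in the document: both arms improve by g SD over three months, exits occur at a fraction f of that improvement, and withdrawal is w₁ in one arm and w₂ in the other.

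Shift in the contrast: g × (1 − f) × (w₂ − w₁).

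- g = 0.5, f = 1/3, 5% against 15%: 0.5 × 0.667 × 0.10 = 0.033 SD; type I error 0.052.
- g = 1, f = 1/3, 5% against 25%: 1 × 0.667 × 0.20 = 0.133 SD; type I error about 0.09.

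The bias is negligible in the mild case and visible only with a marked imbalance.

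**The case against.** The strongest reply is that the planned test is defined on last follow-up, the exit PANSS supplies that value, and month-1 and month-2 scores are kept as well. Patients with a post-baseline score can be analysed as randomised, and the repeated-measurements analysis uses every observed visit. This stands. A reader might infer that the intention-to-treat analysis cannot be carried out; the document does not support that. A reader might also infer that recovering month-3 visits would raise the analysed number from 36 to 40 per arm and so lower the detectable effect. That fails for the same reason: withdrawn patients with an exit score already count.

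Second, the withdrawal section does not say that stopping tablets ends follow-up. The adverse-reactions section has patients interrupt study medication around procedures and resume, and the per-protocol analysis above 90% adherence implies that poor adherers stay in the trial. This also stands. The point is confined to patients withdrawn from the study.

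Third, the consent wording can be over-read as compelling assessments after consent is withdrawn. The text says outcomes *should* be assessed, and the trial is placed under the Declaration of Helsinki. This is a minor matter of wording.

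Fourth, a condensed article leaves procedures to the full protocol, and the PANSS sentence uses *and* where the footnote uses *or*. The *and* leaves some room for a retained month-3 visit. But the either/or rule is stated for the month-3 column, the cognitive tests and the blood samples, and nowhere is a month-3 PANSS expressly provided after withdrawal. The point therefore concerns a rule the article states.

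**Conclusion.** The concern holds in a limited form. As written, the exit assessment replaces month 3 for patients who are withdrawn by the psychiatrist and still consent, and their early score then represents a 3-month outcome that was not observed. The comparison can be run, but for these patients it answers a different question from the one in the outcome section.

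The size is modest at the plan's own 10% allowance: power about 0.78 against 0.83. It grows to about 0.71 at 20%. Both figures assume equal withdrawal, one third of the effect at exit and an unchanged SD. The 10% is a planning allowance that does not separate the two kinds of withdrawal, so only part of it would be recoverable. The 0.83 assumes that 0.66 is the month-3 effect across everyone randomised. If patients lose the effect after stopping treatment, month-3 data will not restore that power, but they will still measure the outcome named. Bias needs unequal withdrawal and could run from negligible to about 0.13 SD in the cases shown.

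The change is worth making because it is cheap and cannot be made after the visits are missed.

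**What to change.** 1. Leave the clinical decision to withdraw as it is.
2. In the withdrawal section, separate the two events for data collection. If consent is retained, keep the already scheduled PANSS visits, at least month 3, in addition to the exit assessment, and use the month-3 value in the intention-to-treat analysis. If consent is withdrawn, do an exit assessment only if the patient agrees.
3. Align the follow-up text, the Table 1 footnote and the immunological-measurements section with this rule, and reconcile *and* with *or* for withdrawal.
4. Reconcile the 3-month change in Study outcomes with last follow-up in Study size and Data analysis, so that one time point defines the primary comparison.

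Cost: a wording change in the protocol and consent form, and a few attendances at visits already planned (at most about 8 patients under the 10% allowance, fewer once withdrawals of consent are set aside). Some off-treatment values will enter the estimate, which is inherent in an intention-to-treat comparison.

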### Study size

The planned number of patients to be included in this trial is 80, 40 in each arm. This is sufficient to show a statistically significant difference between the intervention arms of effect size (Cohen's *d*) ≥ 0.66 for the change in total PANSS score from baseline to last follow-up. It is based on an alpha of 0.05, a power (1-beta) of 0.8 and a two-sided unpaired t-test. Further, we accounted for 10% withdrawal. It should be noted that the power of the repeated measures analyses is considerably higher.

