### Randomized intervention

Patients will be randomized in a 1:1 ratio to either supplementation of acetylsalicylic acid or placebo in addition to their current antipsychotic treatment. Randomization will be performed in strata of psychiatric center (tertiary or non-tertiary) and relative TH-2 reactivity (high/low), delineated by the median IFN-γ/IL-4 ratio. To this end a computer-generated list will be produced with allocation codes in random order, balanced in the four strata by using permuted blocks. The aspirin dose is based on a trade-off between a dose that has a relatively low risk of gastro-intestinal toxicity in young persons, and the dose that is presumed to be anti-inflammatory, the latter being adopted from therapeutic doses used in the treatment of musculo-skeletal disorder[18]. Placebo will be identically packaged, looking and tasting tablets. For optimal gastro protection, all patients (also those randomized to placebo) will be given 40 milligrams of pantoprazole daily[19].

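### The unconditional claim that the repeated-measures analyses have considerably more power than the t-test is unsupported, and an unadjusted arm effect averaged over visits has less power if the effect builds up gradually

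*Protocol article*

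**What the plan says.** Study size (Protocol article): "The planned number of patients to be included in this trial is 80, 40 in each arm". The detectable effect is a Cohen's d "≥ 0.66 for the change in total PANSS score from baseline to last follow-up", and on the method: "It is based on an alpha of 0.05, a power (1-beta) of 0.8 and a two-sided unpaired t-test". It continues: "Further, we accounted for 10% withdrawal". The paragraph closes with "It should be noted that the power of the repeated measures analyses is considerably higher".

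Study outcomes: "The primary outcome of this trial is the 3-month change in positive and negative symptoms on the total PANSS score".

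Data analysis names the two-sided unpaired t-test of the change to last follow-up first. It then states, as an addition, that "all outcomes will be analyzed as dependent variables in repeated measurements analyses with treatment arm as the independent variable". Time, an arm-by-time term, baseline adjustment and a correlation structure are not mentioned.

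Table 1 (Follow-up assessments) places the PANSS at baseline and months 1, 2 and 3, and the cognitive tests at baseline and month 3 only.

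**The concern.** More visits do not by themselves give more power for a 3-month effect. A treatment-arm effect across visits is an average over those visits. Averaging reduces variance, but it also reduces the effect if months 1 and 2 show less of it than month 3. Which of the two prevails depends on the time course, the correlation and the model, and the article states none of these.

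Two things are at stake. A reader may credit the trial with a power margin that it does not necessarily have. And an analysis described as the more powerful one may be read as evidence on the primary outcome although, as worded, it need not estimate the 3-month change.

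**Working it through.** **Inputs from the article.** 40 per arm, 10% withdrawal (36 evaluable per arm), d = 0.66 on the change score, two-sided alpha 0.05, power 0.80, unpaired t-test, PANSS at baseline and months 1, 2 and 3.

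**Assumptions, because the article gives no figure.** Common variance σ² at each visit, compound symmetry with correlation ρ, complete data in the 36 per arm, and a stated share of the month-3 effect present at months 1 and 2.

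**1. The article's own figure.** Normal approximation: n = 2 × ((1.960 + 0.842)/0.66)² = 36.04 per arm. Allowing for withdrawal, 36.04/0.9 = 40.04, so 40 per arm and 80 in total. This reproduces. With the noncentral t distribution, 36 per arm at d = 0.66 gives power 0.789. That is the comparator below.

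**2. Unadjusted arm effect on the mean of the three change scores.**
- Variance of the month-3 change: 2σ²(1 − ρ).
- Variance of (mean of months 1 to 3, minus baseline): (4/3)σ²(1 − ρ).
- Ratio: 2/3, whatever ρ is.
- Standardised effect: 0.66 × m/√(2/3), where m is the mean share of the month-3 effect over the three visits.
- Break-even with the t-test: m = √(2/3) = 0.82.

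| Share at months 1, 2, 3 | m | Standardised effect | Power |
|---|---|---|---|
| t-test of month-3 change | – | 0.660 | 0.79 |
| 1, 1, 1 | 1.00 | 0.808 | 0.92 |
| 0.8, 1, 1 | 0.93 | 0.754 | 0.88 |
| 0.5, 0.75, 1 | 0.75 | 0.606 | 0.72 |
| 1/3, 2/3, 1 (linear) | 0.67 | 0.539 | 0.62 |

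Under a first-order autoregressive structure with ρ from 0.3 to 0.8, power is 0.94 to 0.96 with full effect from month 1 and 0.65 to 0.71 with linear build-up. The direction is the same.

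**3. Month-3 contrast with baseline adjustment.** With complete data and a model with visit, arm-by-visit and baseline (its coefficient allowed to differ by visit), this is the analysis of covariance at month 3. Its residual variance is σ²(1 − ρ²), so the standardised effect is 0.66 × √(2/(1 + ρ)):
- ρ = 0.3: 0.819, power 0.93
- ρ = 0.5: 0.762, power 0.89
- ρ = 0.7: 0.716, power 0.85

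The gain over 0.79 comes from baseline adjustment, not from the visits at months 1 and 2.

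**4. Cognitive tests.** With one baseline and one follow-up value and complete data, the arm-by-time test equals the t-test of the change. Repeated measures bring no gain there.

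**The case against.** **The claim can be true.** The full effect need not be present at month 1: with 80% there and all of it from month 2, power is 0.88. Other repeated-measures models can also gain under linear build-up. A linear arm-by-time slope gives 0.83 under compound symmetry. A baseline-adjusted mean of the follow-ups gives 0.91, 0.81 and 0.73 at ρ = 0.3, 0.5 and 0.7, partly because of the adjustment. This stands. A reader might infer that the sentence is false unless the whole effect is present by month 1, and the figures do not support that. What remains is that an unconditional statement is made whose truth depends on conditions the article does not give.

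**The model may be fuller than its description.** In a condensed article, naming the arm may only identify the between-patient factor, and time terms may be in the full plan. This stands too. A reader might infer that arm is the only term, or that baseline is one of the outcomes, but the text does not say so. The point about the 3-month change applies to the wording shown. The power sentence is different: it is a positive statement, not an omitted detail.

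**The hierarchy is fairly clear.** The t-test sizes the trial and is named first; repeated measures are additional. A reader might infer two competing primary tests and a type I error of about 0.08 to 0.10. That figure requires a rule that success on either test suffices, and the article states no such rule.

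**Earlier visits help when data are missing.** With 10% withdrawal planned for, months 1 and 2 can inform the month-3 contrast. That is a fair reason to use the model, but it does not establish that power is considerably higher.

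**Conclusion.** The concern holds in a limited form. The power sentence is unsupported as written. For an unadjusted arm effect averaged over visits it is false under gradual build-up: power falls from 0.79 to 0.72 or 0.62 in the two gradual cases shown. For that analysis under compound symmetry, a gain needs an average of more than 82% of the month-3 effect over the three visits. As worded, the arm effect also need not estimate the primary outcome unless the effect is constant over follow-up.

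The power figures rest on 36 per arm, complete data, d = 0.66 at month 3, and assumed correlations and time courses. The sample size is unaffected: 80 is justified by the t-test alone, and that test does address the change in total PANSS.

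**What to change.** In Study size, delete the closing sentence, or qualify it by stating the model, the correlation and the effect time course under which the higher power is claimed.

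In Data analysis, specify for total PANSS a repeated-measures model with visit, arm-by-visit and baseline PANSS, and name its month-3 arm contrast as the single test of the primary outcome. Report the unadjusted t-test of the change as supportive. For the cognitive tests, claim no power gain from repeated measures.

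The cost is wording in two sections, settled before unblinding. All the data needed are already collected under Table 1, and no patients or visits are added. The power statement becomes more modest, but the primary test itself gains over the unadjusted t-test at the correlations shown in the working.

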### Data analysis

The statistical significance of the difference in the change in total PANSS score, its subscores, cognitive functions, immunological parameters from baseline to last follow-up between the arms and psychoactive medication will be tested using a two-sided unpaired t-test and its magnitude will be supplied with a 95% confidence interval. In addition, all outcomes will be analyzed as dependent variables in repeated measurements analyses with treatment arm as the independent variable. To study whether the potentially beneficial effect of acetylsalicylic acid is modified by initial relative TH-2 reactivity, we will repeat the analyses in strata of IFN-γ/IL-4 ratio The analyses will primarily be 'intention-to-treat'. In addition, a per protocol analysis will be performed on those who showed more than 90% adherence. If despite randomization important baseline differences in prognostic factors exist, adjustments will be made by including the corresponding variables as independents in the multivariable models. Finally, the change in psychopathological symptoms will be related to the change in immunological parameters using multivariable regression models. In these analyses adjustments for confounders will be made when appropriate.

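### Cytokine outcomes are tested by an unpaired t-test on change with no transformation or baseline adjustment named, which is inefficient if the ELISA values are clearly right-skewed

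*Protocol article*

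**What the plan says.** Study outcomes in the protocol article lists "immunological parameters (γ-interferon, IL-4, IL-6 and IL-12") among the secondary outcomes. Under Immunological measurements, "Cytokine levels in culture supernatants will be analyzed by ELISA"; in addition, "In vivo cytokine production will be analyzed by determining cytokine levels in plasma samples obtained at the same time points". Table 1 places these measurements at the start of run-in and at two and three months, so each randomized patient should have a baseline value.

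Data analysis then sets one test for symptoms, cognition and cytokines alike: "cognitive functions, immunological parameters from baseline to last follow-up between the arms and psychoactive medication will be tested using a two-sided unpaired t-test". The size of the difference is also to be reported: "its magnitude will be supplied with a 95% confidence interval". A second analysis is added: "all outcomes will be analyzed as dependent variables in repeated measurements analyses with treatment arm as the independent variable". Neither sentence gives a scale, a transformation or a baseline covariate for the cytokines. Adjustment is foreseen only if important baseline imbalances appear. The section closes by relating symptom change to change in the immunological parameters by regression.

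**The concern.** A PANSS total and a cytokine concentration are different kinds of variable. A concentration cannot fall below zero. If it varies several-fold between patients, its spread grows with its level, and a drug that acts proportionally moves high producers by far more units than low producers. A difference in mean concentration change then depends heavily on a few patients, and those same patients become high-leverage points in the symptom-cytokine regression.

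The protocol's own mechanism is also relative. The Background argues in terms of TH-1 activity against TH-2 activity and uses the IFN-γ/IL-4 ratio. Proportional changes become differences only on the log scale.

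At stake is the mechanistic half of the trial. The abstract gives knowledge of pathogenesis as one of two aims, and the study objectives name immunological parameters. The sample size was set for PANSS only, so a null cytokine result could partly reflect an inefficient analysis.

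**Working it through.** **1. The plan's own figure.** Study size states that "The planned number of patients to be included in this trial is 80, 40 in each arm", for d = 0.66, two-sided alpha 0.05, power 0.8 and 10% withdrawal. The normal approximation gives n per arm = 2(1.960 + 0.842)²/0.66² ≈ 36.04. Both arms together need 72.08, and 72.08/0.9 = 80.1, so 80 reproduces. Evaluable patients per arm: 40 × 0.9 = 36. No power figure is given for any cytokine.

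**2. Assumed inputs (none is in the article).** Log-normal values at baseline and follow-up; equal log-scale SD s at both times (0.6, 0.8 or 1.0); log-scale correlation 0.6; treatment multiplies the follow-up value by 1.6 (rise) or by 1/1.6 = 0.625 (fall).

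**3. Log-scale tests in closed form.** The log effect is ln 1.6 = 0.470.
- t-test on log change: SD of change = s√(2(1 − 0.6)) = 0.894s. Standardized effects are 0.88, 0.66 and 0.53 for s = 0.6, 0.8 and 1.0. With 36 per arm the noncentral t gives power of 96%, 78% and 59%.
- ANCOVA on log values: residual SD = s√(1 − 0.6²) = 0.8s. Standardized effects are 0.98, 0.73 and 0.59, and power is about 98%, 87% and 69%.

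**4. Simulation, including the t-test on concentration change.** Power in %, repeatable to within about 2 points:

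| Effect | s | Concentration change | Log change | Log ANCOVA |
|---|---|---|---|---|
| 1.6-fold rise | 0.6 | 93 | 96 | 98 |
| | 0.8 | 67 | 79 | 87 |
| | 1.0 | 41 | 59 | 68 |
| 1.6-fold fall | 0.6 | 77 | 95 | 98 |
| | 0.8 | 49 | 79 | 86 |
| | 1.0 | 28 | 59 | 68 |

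**5. Separating the two sources of loss.** Scale alone (column 4 minus column 3) costs 3, 12 and 18 points for a rise, and 18, 30 and 31 for a fall. Baseline adjustment (column 5 minus column 4) accounts for a further 2, 8 and 9 points for a rise, and 3, 7 and 9 for a fall. A fall does worse on the concentration scale because the same log effect is smaller in units: mean follow-up shifts by 0.375 of its level (1 − 0.625) rather than by 0.6.

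**6. Mild skew.** A second simulation fixed the log effect so that the log-change t-test had d = 0.66 (power about 79%), with correlations of 0.3 to 0.7. At s of 0.5 or less, the concentration-change test lost about 0 to 4 points for a rise. For a fall it lost 7 to 8 points at s = 0.3 and 15 to 16 at s = 0.5.

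**7. Influence and validity.** In that second simulation, at s = 1.0 and correlation 0.5, the three most extreme of 72 patients carried a median 57% of the squared deviations of change, against 23% for normal data. With no treatment effect, the concentration-change test rejected in 3.3% to 5.1% of trials for s from 0.3 to 1.5.

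**The case against.** The strongest reply is that the article never says the changes are taken on untransformed concentrations. A t-test on log change would also satisfy the sentence, the article is a condensed account, and an analysis plan that is not shown may set the scale and the handling of undetectable values. This stands as a limit: a reader might infer that the plan prescribes untransformed values, but that is inferred from silence. It does not dispose of the point. The article commits these outcomes to a named test on change, and even a log-change t-test leaves the collected baseline unused as a covariate.

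Second, skewness and a proportional drug effect are assumed. This also stands. A reader might infer that a substantial power loss is established, but the article gives no cytokine SD, correlation or detection limit, and for a rise with mild skew the loss is close to nil.

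Third, setting the concentration-change t-test directly against log-scale ANCOVA credits the log scale with a gain that partly comes from baseline adjustment. This is correct: for a rise it is 8 of 20 points at a log-scale SD of 0.8 and 9 of 27 at 1.0. The two parts are therefore shown separately above.

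Fourth, a reader might think that the effect modifier should be logged too. The IFN-γ/IL-4 ratio is used only as high and low strata cut at the median. Taking logs keeps the order of patients, so no patient changes stratum.

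The added repeated measurements analysis is not an answer, since it names no scale or baseline covariate either.

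**Conclusion.** The point holds in conditional form. For the secondary cytokine outcomes the protocol article fixes an unpaired t-test on change and names neither a transformation nor a baseline adjustment. If that means change in measured concentration, and if the values are log-normal with a log-scale SD of 0.8 to 1.0, the scale alone costs about 12 to 18 points of power for a 1.6-fold rise and about 30 for a 1.6-fold fall. Leaving out the baseline covariate costs a further 7 to 9 points. These figures rest on 36 evaluable patients per arm and the assumed correlation of 0.6.

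The consequence is lost precision and the lack of a fold-change estimate. Validity is not at issue, because type I error stays at or below about 5%. The sample size and the primary PANSS comparison are untouched. The change is worth making because it is almost free and because settling the scale before unblinding rules out choosing it after seeing the results.

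**What to change.** In Data analysis, state that IFN-γ, IL-4, IL-6 and IL-12, in supernatant and in plasma, are analysed on the log scale, either by ANCOVA or in the repeated measurements model already planned, with log baseline as covariate. Report treatment effects as geometric mean ratios with 95% confidence intervals. Use log changes of the cytokines in the symptom-cytokine regression. Leave the IFN-γ/IL-4 strata as they are.

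The cost is a few sentences and no new data. There are two downsides. Effects are expressed as fold changes rather than in absolute units. Values below the detection limit also need a rule set in advance: treat them as left-censored, for example, or analyse by rank if they are frequent. If the unseen analysis plan already specifies log-scale analysis, a clause saying so settles the scale, and only the baseline covariate remains to be confirmed.
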